### Procedure

Background data will be gathered via medical records and questionnaires. Medical and nursing staff will gather daily routine data regarding pain, anxiety, and agitation, along with any other information relevant to usual care in the ICU. Collection of data concerning pain, anxiety and agitation will be carried out by the staff who regularly care for the patients. For this study these caregivers have received special training. Data about the outcome indicators will be collected using questionnaires 1 week, 6 months and 12 months after discharge. It should be emphasized that participants in the ICU group will be asked one week after discharge to make an assessment of both their current HR-QOL and their HR-QOL, pain, anxiety and agitation intensity, before admission to the ICU. One week after ICU discharge, patients in the ICU group will be contacted and interviewed. The interviews will be carried out only if the patients are physically and psychologically fit to be interviewed. If necessary, help will be provided in filling out the questionnaire. All data will be collected using face-to-face (baseline) and telephone (follow-up) interviews and will be collected by 4 trained interviewers. The baseline interviews with all critically ill patients will take place in the hospital. All other interviews for both groups will take place by telephone. The SF36 and HADS-D will be mailed to all participants. In order for them to prepare themselves for the interview, both groups will be informed of the general nature of the questions ahead of time. Because unanswered questions would affect the evaluation of the questionnaires, an interviewer will check to ensure that all questions have been answered, and follow up in cases where information is lacking. If questionnaires are not returned, reminders will be sent to the participants.

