
### Study Aims

The overall aim of this study is to identify how an ICU stay influences an older person's experiences later in life. The study addresses the following research questions: (1) Does an ICU stay influence the pain, anxiety, and agitation experienced by older critically ill patients after discharge, and at 6- and 12-month follow-up? (2) Do the pain, anxiety and agitation experienced by older critically ill patients during an ICU stay affect their experiences of these symptoms after discharge, and at 6- and 12-month follow-up? (3) Does an ICU stay affect the health-related quality of life (HR-QOL) of older critically ill patients after discharge, and at 6-and 12-month follow-up? (4) What is the relation between the ICU stay and subsequent use of the health care system (readmissions, general practitioner visits, rehabilitation, length of hospital stay), medication use, living situation, and survival as experienced by older critically ill patients after discharge, and at 6- and 12-month follow-up?

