## Methods/Design

### Design

A prospective longitudinal study will be conducted in older critically ill patients admitted to the ICU. Data will be collected over a period of two years at the following intervals: during ICU admission and 1 week, 6 months and 12 months after hospital discharge. A flow chart of the study is presented in Figure 1.

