### Outcome indicators after discharge

In line with the study aims, the following outcome indicators will be measured in both the ICU group and the comparison group: (1) pain, anxiety and agitation, (2) HRQOL and (3) use of the health care system (readmissions, general practitioner visits, rehabilitation, length of hospital stay), medication use, living situation and survival. Pain intensity will be measured with a numeric scale (NRS) (0 = no pain to 10 = worst possible pain) [29,30], and pain frequency with a Likert-type scale (never, seldom, occasionally, often, always). Anxiety will be assessed using a numeric rating scale (0-10) and the Hospital Anxiety and Depression Scale (HADS-D), which uses two subscales--an anxiety scale (HADS-A) and a depression scale (HADS-D). Internal consistency (Cronbach's alpha) is 0.80 for HADS-A and 0.81 for HADS-D. The test-retest reliability shows the correlations r = 0.81 for HADS-A and r = 0.89 for HADS-D [35]. Agitation will be measured using the Confusion Assessment Method (CAM). The German or French Short Form of the Confusion Assessment Method (CAM) [36], including a telephone version for the 6- and 12-month follow-ups [37], will be used for all participants. The inter-observer reliability of the CAM is high (kappa = 0.81-1.0) [38]. Health-related quality of life (HR-QOL) will be assessed using the component scores of the Short Form 36 Health Survey (SF-36). As a comprehensive, generic, 36-item instrument, the SF-36 concentrates on the subjective evaluation of health: 1) physical function, 2) physical role function, 3) bodily pain, 4) general health perceptions, 5) vitality, 6) social role function, 7) emotional role function, and 8) mental health. The items vary from yes/no questions to those offering 6 levels of choice. All subscales have been adapted to yield assessment values between 0 and 100. The health care system assessment will include the number, cause, and length of hospital admissions and stays using APACHE-Diagnosis non-operative and operative diagnoses (1) cardiovascular, 2) respiratory, 3) gastrointestinal, 4) neurological, 5) sepsis, 6) trauma, 7) metabolic, 8) haematological, 9) other, 10) cardiologic surgery, 11) respiratory surgery, etc., the number and the length of rehabilitation periods (location, length, ambulatory, stationary, discharge location) and the number of GP visits. Medication therapy, and mortality incidence, will be collected from all subjects in the ICU and comparison groups over the course of the study. Medication therapy includes all sedative, analgesic, antipsychotic, psychotropic, steroidal, and vasoactive medications. The cumulative amount of medication will be recorded. Mortality incidence will be determined based on survival rates. For all instruments, French and German versions will be available. Translation of the SF-36 into German and French was done according to the Translation Protocols of the International Quality of Life Assessment Group [39,40]. The SF-36 Health Survey and the HADS-D have been used in a range of intensive care-related studies [5,41,42]. An overview of all measurements is summarized in Tables 1 and 2.

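### Health-care and medication use before the ICU is not recorded, and the cumulative medication count has no fixed start, so question 4 cannot separate continued use from new use

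*Protocol article*

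**What the plan says.** **The question.** Study Aims, question 4: "What is the relation between the ICU stay and subsequent use of the health care system". It names readmissions, GP visits, rehabilitation and length of hospital stay, and adds medication use, living situation and survival, with 6- and 12-month follow-up.

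**Pre-ICU information.** Procedure: one week after discharge the ICU group rates its current HR-QOL and also "their HR-QOL, pain, anxiety and agitation intensity, before admission to the ICU". Background data adds, at baseline for all participants, co-morbidities and items on need for assistance, home care and residence. It does not say whether these items refer to the time before admission or to the present.

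**The reference group.** Participants and Setting: a convenience sample of older people from the Swiss population with no ICU admission in the last 15 years, matched on age and gender.

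**The medication count.** Under the heading "Outcome indicators after discharge", data on drug treatment and deaths "will be collected from all subjects in the ICU and comparison groups over the course of the study". The drug classes counted include sedatives and vasoactive drugs. As to the summary measure, the section states: "The cumulative amount of medication will be recorded". No start date is given. The Design section places data collection "during ICU admission and 1 week, 6 months and 12 months after hospital discharge".

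**The concern.** The plan sees that later scores need a pre-admission value, and asks for one for the outcomes of questions 1 to 3. It does not do so for the utilisation and medication outcomes of question 4. People who come to need at least 48 hours of intensive care may already have been seeing their doctor more often and taking more drugs than age- and gender-matched people with no ICU stay in 15 years. If so, a higher level at 6 or 12 months would appear even if the ICU stay had changed nothing. This is a data-collection matter: a value that was never asked for cannot be restored by any later model.

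The open start of the medication count is a second source of ambiguity. Sedative and vasoactive drugs are among the classes counted. Whether ICU treatment enters the total could therefore change what the 6- and 12-month figures mean, and comparison participants have no corresponding stay.

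**Working it through.** The plan gives no figure on this point. Its sample-size calculation concerns the prevalence of pain and does not bear on question 4. The check sets the sections side by side.

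**Step 1. Is there a prior-period value for each question 4 outcome?**

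| Outcome | Pre-admission recall (Procedure) | Elsewhere |
|---|---|---|
| GP visits | not listed | a count is measured; no prior period stated |
| Hospital admissions and days | not listed | number, cause and length measured; no prior period stated |
| Rehabilitation | not listed | number and length measured; no prior period stated |
| Medication | not listed | cumulative amount; start not stated |
| Living situation | not listed | residence and home-care items at baseline; reference time not stated |
| Survival | none needed | none needed |

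The gap lies in the first four rows.

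**Step 2. What does a follow-up contrast estimate without these values?** Let b1 and b0 be the mean use per period before the study in the ICU and comparison groups, and d1 and d0 the mean changes afterwards. The difference at follow-up is

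(b1 + d1) − (b0 + d0) = (b1 − b0) + (d1 − d0).

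The part that concerns change after the ICU is d1 − d0. If d1 = d0, the contrast still equals b1 − b0. Age and gender matching makes b1 − b0 zero only if prior use depends on nothing else that differs between the groups. Selection for no ICU stay in 15 years gives no reason to expect that. With neither b1 nor b0 recorded, the two parts cannot be separated. The documents contain no utilisation rates, so b1 − b0 has no value that can be put in.

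**Step 3. Can the week-1 wave serve as b1?** As described, no. ICU patients are interviewed in hospital at that time, and no look-back period is stated for the counts taken then. Use during an acute stay does not measure usual use before it.

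**Step 4. When does the cumulative medication count start?**
- Reading A: "will be collected from all subjects in the ICU and comparison groups over the course of the study", joined to data collection that begins in the ICU (Design), lets ICU drugs enter the total.
- Reading B: the heading "Outcome indicators after discharge" limits the count to the time after discharge.

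Reading B still leaves two dates, because discharge has two meanings. In Design, the 1-week, 6-month and 12-month points follow hospital discharge. In the Abstract, the 6- and 12-month points follow ICU discharge. In Table 2 and in the interview instructions under Procedure, the 1-week point follows ICU discharge. If the clock starts at ICU discharge, the rest of the index hospital stay, with its drugs and bed days, falls inside the later use. If it starts at hospital discharge, it does not. The text thus allows three start points: ICU admission, ICU discharge and hospital discharge.

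**The case against.** The best case for the plan has four parts.

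1. The article is condensed and the questionnaire is not shown. The sentence on pre-admission recall is introduced as a point of emphasis and does not claim to be exhaustive, so look-back items on service use may exist. This stands as a limit on certainty. Still, the article lists what is recalled and describes each utilisation measure, and no prior period appears in either place.

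2. The plan has a reference: the comparison group is there to help interpret trends, and random effects models are named for the longitudinal data. Question 4 asks only for a relation. Co-morbidities and assistance items are also taken at baseline, and both groups are subject to exclusions for dementia, psychotic illness and potentially terminal illness, which may narrow differences in prior use. A reader might infer that question 4 has no pre-ICU reference at all, or cannot be answered. The documents do not support that: survival needs no prior value, living situation is partly covered, and an association can be described. What remains is that the health-care and medication part cannot be split into continued and new use.

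3. A reader might infer that ICU drugs are counted as later use. No section says so. The heading points the other way, outcome data are to be collected by questionnaire at 1 week, 6 months and 12 months, and Table 1 on the ICU stay has no medication row. The defect is an undefined start. Nor is use before admission itself counted as subsequent use, since nothing from that period is collected. The problem is confounding by prior use.

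4. The term readmissions fits comparison participants poorly, and Tables 1 and 2 have no rows for service use or medication. Neither is a substantive fault: the outcome section already measures the number, cause and length of all hospital admissions in both groups, and the missing rows show only an incomplete overview.

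**Conclusion.** The point holds for health-care use and medication use within question 4. As described, the plan records no pre-admission level for GP visits, hospital admissions, rehabilitation or regular medication. Its comparison group does not make up for this, so a difference at 6 and 12 months cannot be divided into prior use that continued and use that is new after the ICU. The size of the bias cannot be computed from the documents. An upward direction is plausible, given how the comparison group is selected, but it is not documented. The start of the cumulative medication count is ambiguous, with wording that fits more than one date.

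The conclusion rests on two assumptions: that the questionnaire follows the article's list of recalled items, and that prior use may differ between the groups beyond age and gender. It is a worthwhile, inexpensive improvement to make before data collection, and it leaves the rest of the design as it is.

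**What to change.** 1. At the week-1 interview, ask the ICU group about GP visits, hospital admissions, rehabilitation and regular medication in the 6 months before ICU admission. Ask the comparison group the same about the 6 months before its first interview. Six months matches the interval between the two later waves.
2. Use these values as the baseline in the question 4 models, and state this in the plan.
3. Start the cumulative medication, hospital-day and rehabilitation counts at one common point in both groups, the first interview. Report amounts from the ICU and the rest of the index hospital stay separately.
4. Use one definition of discharge in the Abstract, Design, Procedure and Table 2.

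Cost: a few added questions at interviews already planned, slightly more respondent burden, and some recall error. The look-back would not remove every difference between the groups, but it would make prior use visible and allow adjustment for it.

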### Ethical Considerations

The study protocol was approved by the Cantonal Ethics Commission of Bern. For the patient interviews during the first week (5 to 10 days) after the ICU stay, patients will be contacted, comprehensively informed about the study--verbally and in writing--and invited to participate. The participants in the comparison group will receive the same information. Study participants agree to participate via a written informed consent form. To ensure confidentiality, all data will be coded, and all personal data will be documented, archived, and analyzed anonymously, making it impossible to determine the identity of the individual participants.

### Data Analysis

The statistical analysis will be performed using the R Project for Statistical Computing. Descriptive statistical analyses (mean, median, interquartile range) will be used to describe and characterize the data. To indicate the strength and direction of relationships between variables, Spearman's rank correlation coefficient for ordinal data and Pearson's product-moment coefficient will be conducted, depending on measurement levels and data dispersion. The Mann-Whitney U Test will be used for continuous data when comparing groups, and random effects models will be used for the longitudinal data. Attrition (i.e., missing data) during the follow-up will be reported.

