## Abstract

**Background:**

Modern methods in intensive care medicine often enable the survival of older critically ill patients. The short-term outcomes for patients treated in intensive care units (ICUs), such as survival to hospital discharge, are well documented. However, relatively little is known about subsequent long-term outcomes. Pain, anxiety and agitation are important stress factors for many critically ill patients. There are very few studies concerned with pain, anxiety and agitation and the consequences in older critically ill patients. The overall aim of this study is to identify how an ICU stay influences an older person's experiences later in life. More specific, this study has the following objectives: (1) to explore the relationship between pain, anxiety and agitation during ICU stays and experiences of the same symptoms in later life; and (2) to explore the associations between pain, anxiety and agitation experienced during ICU stays and their effect on subsequent health-related quality of life, use of the health care system (readmissions, doctor visits, rehabilitation, medication use), living situation, and survival after discharge and at 6 and 12 months of follow-up.

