## Measurements

### Background data

Demographic data include age, gender and marital status. Furthermore, health-related data including Activities of Daily Living (ADL) and co-morbidities will be collected at baseline for all participants. The severity of the patient's condition will be determined using the Acute Physiology and Chronic Health Evaluation (APACHE II) and the Simplified Acute Physiology Score (SAPS II) [27]. The performance of ADL will be measured using items querying the need for assistance with daily activities (home health care, home food delivery, residence in a retirement home or nursing home) and various quality-of-life dimensions such as physical function, physical role function, vitality and social role function (Short Form 36 Health Survey [SF-36]). A scale developed for this study will be used to assess the need for assistance with daily activities (completely dependent; needs support by caregivers and special medical equipment; needs caregivers; independent with medical equipment; completely independent). Co-morbidities will be measured using the International Classification of Diseases (ICD), Version 10 [28].

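### Question 2 and abstract objective 2 ask about an effect of ICU symptoms, but the only method named for relationships is an unadjusted correlation, and severity and pre-ICU symptom levels get no role

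*Protocol article*

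**What the plan says.** **The question.** Research question 2 in Study Aims reads: "Do the pain, anxiety and agitation experienced by older critically ill patients during an ICU stay affect their experiences of these symptoms after discharge", and it extends to 6 and 12 months. Objective 2 in the Abstract is "to explore the associations between pain, anxiety and agitation experienced during ICU stays and their effect on subsequent health-related quality of life", and goes on to care use, living situation and survival. The Background section is more openly causal: it contrasts the study with earlier work by asking whether acute ICU experience can bring about chronic conditions. Other wording is softer. Abstract objective 1 is "to explore the relationship between pain, anxiety and agitation during ICU stays and experiences of the same symptoms in later life", and the Discussion speaks of associations.

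**The method.** The Data Analysis section states: "To indicate the strength and direction of relationships between variables, Spearman's rank correlation coefficient" (for ordinal data) or Pearson's coefficient, the choice depending on measurement level and spread. It adds the Mann-Whitney U test for group comparisons and says that "random effects models will be used for the longitudinal data". It assigns no method to a numbered question and names no covariate, partial correlation or adjusted model.

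**What is collected.** Under Background data: "The severity of the patient's condition will be determined using the Acute Physiology and Chronic Health Evaluation (APACHE II") and SAPS II; co-morbidities are also recorded there. Under Procedure, ICU patients are asked one week after discharge to recall their quality of life, pain, anxiety and agitation before admission. The Data Analysis section mentions none of these.

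**The concern.** A patient who was in pain or anxious before admission is likely to report the same in the ICU and a year later. A sicker patient may have more symptoms at both times. Either pattern produces a correlation between ICU and later symptoms even if the ICU experience itself changes nothing, and a bivariate coefficient cannot tell these explanations apart.

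What is at stake is the study's distinctive claim, that acute ICU experience has lasting consequences. The comparison group does not help here: it has no ICU symptoms, so question 2 can be answered only within the ICU group, where confounding by severity and prior symptoms operates. A larger sample does not help either, because it estimates the confounded quantity more precisely.

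**Working it through.** **1. The plan's own figure.** Participants and Setting gives 81 to 96 patients for a 95% confidence interval of total width 0.20 around a pain prevalence of 0.30 to 0.50. With n = 1.96² × p(1 − p) / 0.10²:

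- p = 0.30: 3.8415 × 0.21 / 0.01 = 80.7, i.e. 81.
- p = 0.50: 3.8415 × 0.25 / 0.01 = 96.04, i.e. 96.

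The figure reproduces. It concerns the precision of a prevalence and does not bear on question 2. It supplies only the target of 100 patients (150 recruited to allow for loss).

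**2. Which method serves question 2?** The term that Data Analysis attaches to the correlation coefficients, relationships between variables, is the one abstract objective 1 uses for ICU and later symptoms. On wording, the correlations are the natural candidate. But the outcomes of question 2 are measured repeatedly (1 week, 6 and 12 months), so the random effects models could serve it too. The text leaves this open, and gives neither method an adjustment.

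**3. Size under assumptions.** The documents give no correlation between severity or pre-ICU level and symptoms, so a range is assumed. With one confounder S and no direct link between ICU symptom X and later symptom Y:

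r(X,Y) = r(X,S) × r(Y,S)

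The probability of rejection at two-sided 5%, by Fisher's z with standard error 1/√(n − 3), is

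Φ(δ − 1.96) + Φ(−δ − 1.96), where δ = atanh(r) × √(n − 3).

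Example at n = 100 and assumed correlations of 0.4: r = 0.4 × 0.4 = 0.16; atanh(0.16) = 0.1614; δ = 0.1614 × √97 = 1.589; Φ(−0.371) + Φ(−3.549) = 0.356.

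| Assumed correlation of S with both X and Y | Spurious r | Rejection, n = 100 | Rejection, n = 150 |
|---|---|---|---|
| 0.2 | 0.04 | 7% | 8% |
| 0.3 | 0.09 | 14% | 19% |
| 0.4 | 0.16 | 36% | 50% |
| 0.5 | 0.25 | 71% | 87% |

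Two independent confounders add. Severity at an assumed 0.3 and pre-ICU level at an assumed 0.5 give r = 0.09 + 0.25 = 0.34, and about 94% rejection at n = 100.

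The distortion is small at 0.2 and serious from about 0.4 upward.

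**The case against.** **The analysis section lists methods and does not map them to questions.** A reader might infer that question 2 is to be judged by correlations alone. The text does not say so. Random effects models are planned, the outcomes are longitudinal, and such models can carry covariates. This stands, and it is why the point is confined to what is named for relationships and to the missing link between the models and question 2.

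**A covariate list is commonly left to the full protocol or analysis plan.** This is also correct, and the lack of a list would be no finding by itself. But the article goes further than silence: it names an unadjusted method for relationships while asking about an effect. That choice can be judged as it stands.

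**The aims are partly exploratory, and correlations suit exploration.** This is fair for the abstract's objective 1. It does not cover question 2 or the causal wording in Background.

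**The size is hypothetical.** This stands. The confounder correlations are assumed, and the rejection rates presuppose a 5% test of each coefficient, whereas the plan says only that coefficients indicate strength and direction. A reader might infer that severity will show up as a symptom effect; the documents support only that it may. Even the direction is uncertain for agitation: RASS runs from −5 (unarousable) to +4, so sicker, sedated patients could score low.

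**Adjustment has limits.** Pre-ICU values are recalled at the same interview as the first outcome, after the ICU stay, and current state may colour recall. Sedatives and analgesics may be responses to the symptoms, so adjusting for them could remove part of the effect sought; Table 1 also lists no medication for the ICU stay. Neither that adjustment nor any particular coding of ICU exposure is called for.

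**Conclusion.** The point holds in a limited form. Question 2 and abstract objective 2 ask about effects; the only method named for relationships is unadjusted; the random effects models are neither tied to this question nor given covariates; and severity, co-morbidity and recalled pre-ICU status are collected without a stated role. Followed as written, the plan may mix any effect of ICU symptoms with persistence of earlier symptoms and with illness severity.

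The size depends wholly on assumed correlations. For one confounder, at n = 100, the false-positive rate runs from close to nominal (7% at 0.2) to 71% (at 0.5). The calculation assumes no true link, equal correlations with both symptoms, and a two-sided 5% test.

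The documents do not support reading this as an arithmetic error, as a decision to rely on correlations only, or as proof that bias will occur. It is an analysis choice that should be improved, and the means are already in the study.

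**What to change.** In Data Analysis, state that question 2 and abstract objective 2 are answered within the ICU group by the planned random effects model: the outcome at 1 week, 6 and 12 months on ICU symptom exposure and visit, adjusted for

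- the recalled pre-ICU value of the same outcome where collected (pain, anxiety, agitation, health-related quality of life),
- APACHE II or SAPS II,
- co-morbidity,
- age and sex.

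For objective 2 outcomes without a recalled pre-ICU value, such as care use, use the remaining covariates. Survival is an event and not a repeated score, so it needs a model form of its own with those same covariates.

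Keep the Spearman and Pearson coefficients as descriptive. Say that pre-ICU values are recalled one week after ICU discharge, so adjustment is imperfect, and word conclusions as adjusted associations. If the authors prefer to keep correlations as the main analysis, conclusions should be worded as unadjusted associations and the causal wording in Background and Study Aims softened.

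Cost: analysis wording only. The listed adjustment variables are already collected and the model class is already planned; no new data or patients are needed.
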